**Prognostic question in patients with stroke**

In stroke patients we will evaluate the prognostic value of Copeptin -levels - dependent or independent of sodium imbalance- to predict mortality, ICU stay, length of hospitalization; and morbidity (i.e. outcome after 90 days), as assessed by the National Institute of Health and Stroke Scale (NIHSS, [33], **Appendix 1**) on admission and at day 5, the Barthel index [34] (**Appendix 2**) and Ranking scale [35] (**Appendix 3**) at day 5 of the hospitalization and after a follow-up of 3 months by telephone interview with the patient or if not possible with the nearest relative or health care provider. Further other biomarkers, such as MR-pro ANP, BNP and Troponin will be assessed.

**Prognostic question in neurosurgical patients**

In neurosurgical patients, we will evaluate the prognostic accuracy of Copeptin levels to predict mortality, prolonged ICU stay, length of hospitalization, and morbidity (i.e. outcome after 90 days), as assessed by the Glasgow coma scale **(Appendix 4)** on admission and at day 5**,** Glasgow outcome Scale (**Appendix 5**) and Barthel index at day 5 of the hospitalization and after a follow-up of 3 months by a telephone interview with the patient or if not possible with the nearest relative or health care provider.

**2.3.** We will assess other potential prognostic factors (i.e. pro-atrial natriuretic peptide, B-type natriuretic peptide, procalcitonin, C-reactive protein, IL-6, neuron specific enolase, Cu/Zn superoxide dismutase (Cu/Zn SOD) [36]).

**Overall, the hypotheses are the following**:

1. Copeptin will be a new accurate diagnostic tool to facilitate the differential diagnosis of the etiology of sodium imbalance. Copeptin will have a higher diagnostic accuracy as compared to the routinely used clinical assessment of the extracellular fluid volume by physical examination and laboratory parameters. If copeptin is found to be an accurate tool, we aim to validate our findings in a future intervention study, with the aim to improve the management of neurosurgical and neurological patients with sodium imbalance based on copeptin levels.

2. Copeptin will be a reliable prognostic factor and high-quality predictor for the clinical outcome (i.e. mortality, length of stay in ICU, discharge from ICU, length of hospitalization, clinical outcome within the first week and after three months) of neurological and neurosurgical patients.

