**Statistical Analyses**

Copeptin levels will be assessed in a blinded batch analysis upon completion of the plasma asseveration.

Discrete variables will be expressed as counts (percentage) and continuous variables as means ± standard deviation (SD) or median (interquartile range), unless stated otherwise. First, the overall prevalence of hyponatraemia in neurological and neurosurgical patients will be assessed. Frequency comparison will be done by chi-square test. Two-group comparison of normally distributed data will be performed by Students t-test. For multigroup comparisons, one-way analysis of variance with least square difference for posthoc comparison will be applied. For data not normally distributed, the Mann-Whitney-U test is used if only two groups are compared. The Kruskal-Wallis one-way analysis of variance with Bonferroni’s multiple posthoc test will be used if more than two groups were being compared.

Furthermore we will do a correlation analysis of copeptin levels with sodium levels, serum osmolality and other diagnostic laboratory parameters. Correlation analyses will be performed by using Spearman rank correlation. Levels that are non-detectable will be assigned a value equal to the lower limit of detection for the assay. All testing will be two-tailed and P values less than 0.05 were considered to indicate statistical significance. Scatterplot data will be shown with GraphPad Prism®, Version 4.00 for Windows (GraphPad Software, San Diego California, USA).

We will then compare the diagnostic accuracy of Copeptin levels with other potential biomarkers for sodium imbalance, e.g. atrial natriuretic peptide (ANP) and B-type natriuretic peptide (BNP). The ability of Copeptin to foresee sodium disbalance before it becomes evident by laboratory analysis will be assessed. Therefore we will correlate Copeptin levels with sodium level changes over time.We will construct receiver operating characteristic (ROC) curves and determine the areas under the receiver operating characteristic curve (AUC). The sensitivity and specificity to predict the correct diagnosis of hyponatraemia will be determined, based on the above standardized algorithm [32]. This ascertainment will be done retrospectively on the basis of the review of the complete patient charts by two study investigators, blinded to each other’s diagnosis. Discordant cases will be mutually discussed and resolved. Patients will be managed as usual according to the state of the art treatment.

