**Statistical Analyses**

Basic statistical analyses will be performed as described in the diagnostic study. We will evaluate 18 known predictors (i.e. *age; sex; clinical features* (NIHSS or GCS), *important comorbidities* (coronary artery disease, heart failure, atrial fibrillation, hypertension on admission, previous TIA/Stroke, renal disease, dementia, diabetes); *location of the lesion* (LACS etc.); *stroke subtype by the TOAST criteria*; *therapies* (thrombolysis); *laboratory parameters (*baseline glucose level on admission [46-50], CRP); *body temperature*; *smoking histo*ry), and copeptin levels in our multivariate analysis. All variables will first be tested one by one against the dependent variable unfavorable outcome (defined either as Barthel index <85 or modified Ranking scale 3 to 6) for the presence of a significant association. Only variables significantly associated with the outcome will be assessed in a multivariate model performed separately for each parameter.

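### ICU and hospital stay are outcomes copeptin should predict, but the only methods offered use raw days and do not separate death from discharge alive, which attenuates the association if copeptin predicts both death and longer stay

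*Protocol*

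**What the plan says.** The second overall hypothesis in the protocol (end of section 2.2.2) lists "length of stay in ICU, discharge from ICU, length of hospitalization" as outcomes, beside mortality and clinical outcome. For stroke patients the prognostic question is "to predict mortality, ICU stay, length of hospitalization; and morbidity". For neurosurgical patients it is "to predict mortality, prolonged ICU stay, length of hospitalization, and morbidity". This last wording is the only one that gives stay an adverse direction.

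The Statistical Analyses section of the prognostic study opens with "Basic statistical analyses will be performed as described in the diagnostic study". The section it refers to names the t-test, analysis of variance, Mann-Whitney, Kruskal-Wallis, chi-square and ROC curves, and says "Correlation analyses will be performed by using Spearman rank correlation". The testing level is "All testing will be two-tailed and P values less than 0.05 were considered to indicate statistical significance".

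The regression model has one dependent variable: "unfavorable outcome (defined either as Barthel index <85 or modified Ranking scale 3 to 6". It does not cover stay. No section censors in-hospital deaths in an analysis of stay, treats them as a competing event, ranks them or excludes them.

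**The concern.** A stay can end by discharge alive or by death, and raw days do not tell the two apart. The cohort mixes TIA with intracerebral and subarachnoid haemorrhage and head trauma. A TIA patient who goes home on day 2 and a haemorrhage patient who dies on day 2 therefore have the same value. A split into prolonged and not prolonged ICU stay has the same fault, because the early death falls in the not-prolonged group. Discharge from ICU is equally ambiguous unless it means discharge alive.

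The protocol expects copeptin to predict death. If copeptin also goes with a longer stay, the two effects pull observed days in opposite directions. The better copeptin predicts death, the more its relation with stay is hidden. At stake is the reading of the stay outcomes: a real association could be reported as weak or absent.

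**Working it through.** **The plan's own figures.** The protocol gives no figure for stay. Its sample-size arithmetic holds: 18 predictors × 10, 15 and 20 observations = 180, 270 and 360, and 480 × 0.80 × 0.90 = 345.6, stated as about 350.

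**Assumptions.** None of these comes from the protocol. Let z be standardised log-copeptin.
- Stay: log(stay) = log(9) + b·z + 0.6·e, with e standard normal.
- Death: logit P(in-hospital death) = a + log(OR)·z, with a set to give the chosen mortality.
- Observed days for those who die: min(stay, time to death). Time to death is exponential.

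**True association.** The Pearson correlation of z with log stay is r = b/√(b² + 0.36), and Spearman = (6/π)·arcsin(r/2).
- b = 0.1: r = 0.164, Spearman 0.16.
- b = 0.2: r = 0.316, Spearman 0.30.

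**Observed Spearman with deaths entered at their raw days** (300,000 simulated patients per setting). Each cell gives mean time to death of 3 / 5 / 9 days.

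| Deaths | OR per SD | True 0.16 | True 0.30 |
|---|---|---|---|
| 5% | 2 | 0.10 / 0.11 / 0.12 | 0.23 / 0.25 / 0.26 |
| 5% | 3 | 0.07 / 0.09 / 0.11 | 0.21 / 0.22 / 0.25 |
| 10% | 2 | 0.04 / 0.06 / 0.09 | 0.17 / 0.19 / 0.22 |
| 10% | 3 | 0.00 / 0.03 / 0.06 | 0.12 / 0.15 / 0.19 |
| 20% | 2 | −0.04 / 0.00 / 0.04 | 0.06 / 0.10 / 0.16 |
| 20% | 3 | −0.12 / −0.07 / 0.00 | −0.02 / 0.04 / 0.12 |

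Even with no link between copeptin and death (OR 1), 20% deaths at a mean of 3 days lower 0.16 to 0.11 and 0.30 to 0.21.

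**Second grid.** Time to death is 0.5 days plus an exponential with mean 4, so 4.5 days on average. The odds ratio runs from 1.5 to 3.3. I repeated this grid and the values agreed to within about 0.01.
- True about 0.32: 0.23–0.27 at 5% deaths, 0.03–0.16 at 20%.
- True 0.14: 0.07–0.11 at 5% deaths, 0.03 to −0.10 at 20%.
- True 0.14 with OR 2: 0.09, 0.05, 0.01 and −0.03 at 5%, 10%, 15% and 20% deaths.

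**Against the significance level.** With 346 patients, two-sided p < 0.05 needs |Spearman| of about 1.967/√(344 + 1.967²) = 0.105. A true 0.14 lies above this. The expected 0.09 at OR 2 and 5% deaths lies below it.

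**Other ways of handling deaths** (first grid, b = 0.1, mean time to death 3 days, 5–20% deaths). Survivors only gives about 0.15. Ranking deaths worst gives 0.19–0.27 at OR 2 and 0.21–0.34 at OR 3, which is above the true 0.16 because mortality is now part of the measure.

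**The case against.** The strongest reply is that the protocol never says raw days of all patients will be correlated with copeptin. The prognostic section refers to the basic methods in general and does not mention stay, and the Spearman sentence follows one about sodium, osmolality and other laboratory parameters. A reader might infer that the plan prescribes Spearman for stay and scores deaths as good outcomes. It says neither. Handling of death in an outcome that drives neither sample size nor model could also be settled in a statistical analysis plan that is not shown.

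This stands in part. The link is by general reference, and only the neurosurgical question calls a long stay adverse. What remains is that the protocol names these outcomes and offers no method for them except tests on raw values. Followed as written, it gives the result above.

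Three further points are fair. Every input to the size is assumed. The true correlation uses the stay that patients who died would otherwise have had, which is hypothetical. And the possible remedies answer different questions.

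**Conclusion.** The point holds as a moderate one about the stay outcomes. As the protocol is written, an early in-hospital death enters as a short stay. If copeptin predicts both death and longer stay, the association with stay is attenuated. The direction rests on that condition. The size rests on assumed mortality, stay, time to death and odds ratio, because the protocol gives none of these for its cohort.

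Two stronger readings are not supported:
- That the association will change sign. This needs a weak true association or high early mortality. With a true 0.30 it occurred in the first grid only at 20% deaths, OR 3 and a mean time to death of 3 days. At 5% deaths there was attenuation only.
- That the main prognostic result is compromised. The sample size and the regression model rest on unfavourable outcome (Barthel below 85 or modified Rankin 3 to 6, a range that appears to include death), and mortality is a separate outcome. Neither is touched.

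**What to change.** Define the outcomes as time to discharge alive from ICU and from hospital, with in-hospital death as a competing event. Show cumulative incidence and relate copeptin to it by cause-specific or Fine-Gray regression. Report length of stay in survivors as a description, labelled as conditional on survival. If a worst-rank analysis is used, label it a composite of death and stay and do not offer it as an equivalent measure of stay.

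The cost is some wording and one more standard analysis in SAS or R, both already named in the protocol. Patients are already followed to discharge, and the stay and mortality outcomes already require the dates and vital status. The price is a less direct reading than days of stay.

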**Statistical Analyses**

Basic statistical analyses will be performed as described in the diagnostic study. We will evaluate 18 known predictors (i.e. *age; sex; clinical features* (NIHSS or GCS), *important comorbidities* (coronary artery disease, heart failure, atrial fibrillation, hypertension on admission, previous TIA/Stroke, renal disease, dementia, diabetes); *location of the lesion* (LACS etc.); *stroke subtype by the TOAST criteria*; *therapies* (thrombolysis); *laboratory parameters (*baseline glucose level on admission [46-50], CRP); *body temperature*; *smoking histo*ry), and copeptin levels in our multivariate analysis. All variables will first be tested one by one against the dependent variable unfavorable outcome (defined either as Barthel index <85 or modified Ranking scale 3 to 6) for the presence of a significant association. Only variables significantly associated with the outcome will be assessed in a multivariate model performed separately for each parameter.

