**Inclusion criteria**

1. All consecutive patients who are admitted to the emergency department with an ischemic or hemorrhagic stroke or transient ischemic attach (TIA) according to the World Health organization criteria [37] with symptom onset within the last 3 days.

2. All consecutive patients who undergo intracranial surgery due to

- pituitary tumors

- intracerebral hemorrhage (ICH)

- subarachnoidal hemorrhage (SAH)

- chronic subdural hematoma

- head trauma with contusio cerebri

- intracranial abcesses

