g) Clinical symptoms of hyponatraemia will be evaluated on admission and in case of sodium imbalance in neurological patients. In patients undergoing intracranial surgery we will evaluate clinical symptoms daily. Specifically we will monitor the presence of headache, anorexia, nausea, vomiting, muscle cramps and aches, seizures, confusion, apathetic or lethargic development.
h) Routine/Standard laboratory tests: routine blood sampling including: hematocrit, blood urea nitrogen, bicarbonate, total protein, albumin, uric acid serum and urine electrolytes, urine and serum osmolality, creatinine, lipids, TSH, fT4, T3, and basal cortisol. All blood sampling will be done before any food intake, or smoking, if feasible (both, upright position and smoking will potentially elevate ADH and Copeptin levels). Alternatively, influencing factors will be monitored.
i) Imaging : Computer tomography or MRI of the neurocranium (T1, T2, diffusion-weighted image sequence, with or without contrast), if indicated magnetic resonance angiography or conventional cerebral angiography. We will record the time-points of contrast agent application.

Stroke patients will also be classified on the basis of the vascular territory of the ischemic lesion as follows: total anterior circulation syndrome (TACS), partial anterior circulation syndrome (PACS), lacunar circulation syndrome (LACS), posterior circulation syndrome (POCS).

j) Further investigations: Stroke patients will have neurosonography, echocardiography, standard 12-leaf electrocardiography and 24 –hour electrocardiography and then will be classified by etiology of strokes according to Trial of Org 10172 in acute Treatment (TOAST) stroke subtype classification, which differs between large artery atherosclerosis, cardioembolism, small-artery occlusion, other etiology, and undetermined etiology [42].

Importantly, all these investigations are currently performed in the routine setting. Therefore, no additional costs will be charged to the patient, the health care provider or the health insurances.

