**Measurement of copeptin concentrations**

Copeptin levels will be measured with a new chemiluminescens sandwich immunoassay with a lower detection limit of the assay of 0.4 pmol/L. Therefore, we will sample an additional 7.5ml Plasma EDTA tube which is asserved during the respective routine blood samplings. No additional blood sampling will be done.

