**E. Sample Size considerations**

Design

This is a prospective observational study to evaluate Copeptin as a diagnostic and prognostic marker in neurological and neurosurgical patients.

Analysis

Analysis tools

All relevant clinical and laboratory parameters obtained by interview, clinical tests and reviewing of the medical records will be entered into an Excel® database. Statistical Analysis System (SAS® Institute, Cary, NC, USA) and R for Windows (R Foundation for Statistical Computing, www.r-project.org) will be used for data analysis. Statistical evaluation will include stepwise logistic regression analysis to assess which variables are independently associated with outcome.

Sample size considerations

Our sample size consideration is based on our intention to determine an optimal clinical model to predict the outcome of neurological and neurosurgical patients (based on Barthel index, Rankin scale NIHSS scale and Glasgow outcome scale) (i.e. the prognostic question of the study). To determine an optimal clinical model we will undertake a multivariable regression analysis. It has been demonstrated that multiple regression models with a minimum of 10 to 15 observations per predictor variable reveal good estimates [45]. We will evaluate 18 known predictors (i.e. *age; sex; clinical features* (NIHSS or GCS), *important comorbidities* (coronary artery disease, heart failure, atrial fibrillation, hypertension on admission, previous TIA/Stroke, renal disease, dementia, diabetes); *location of the lesion* (LACS etc.); *stroke subtype by the TOAST criteria*; *therapies* (thrombolysis); *laboratory parameters (*baseline glucose level on admission [46-50], CRP); *body temperature*; *smoking histo*ry) in our multivariate analysis. Therefore, we aim to include a minimum sample size of 180 patients (for 10 observations per predictor) to 270 (for 15 observations per predictor) and a maximum sample size of 360 patients (for 20 observations per predictor). All variables will first be tested one by one against the dependent variable unfavorable outcome (defined either as Barthel index <85 or modified Ranking scale 3 to 6) for the presence of a significant association. Only variables significantly associated with the outcome will be assessed in a multivariate model performed separately for each parameter.

Based on the last year’s data in our hospital, the following number of patients with stroke and neurosurgery will be eligible:

*Patients*

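### One 18-item predictor list, partly specific to ischemic stroke, also serves the neurosurgical patients and omits the indication for surgery, so copeptin's independence from diagnosis cannot be shown in them

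*Protocol*

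**What the plan says.** Section E states the modelling aim as "to determine an optimal clinical model to predict the outcome of neurological and neurosurgical patients". Section 2.2.2 also poses a separate surgical question: "In neurosurgical patients, we will evaluate the prognostic accuracy of Copeptin levels to predict mortality, prolonged ICU stay, length of hospitalization, and morbidity".

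The predictors are fixed in 2.2.2 Statistical Analyses ("We will evaluate 18 known predictors") and repeated item for item in Section E. The list includes lesion location, TOAST subtype and thrombolysis, given as "LACS etc.); *stroke subtype by the TOAST criteria*; *therapies* (thrombolysis". The baseline data section ties the location classes to stroke: "Stroke patients will also be classified on the basis of the vascular territory of the ischemic lesion as follows". It likewise assigns TOAST classes to stroke patients only.

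The surgical inclusion criterion ("All consecutive patients who undergo intracranial surgery due to") covers six indications: pituitary tumors, intracerebral hemorrhage, subarachnoid hemorrhage, chronic subdural hematoma, head trauma with contusion, and intracranial abscess. Indication is not among the predictors. The clinical severity item may be NIHSS or GCS, which is the only concession to surgical patients. The Protocol states no separate surgical list, cohort term or stratification by diagnosis.

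**The concern.** The Synopsis and Section E aim to find variables independently associated with outcome, and the overall hypotheses call copeptin a reliable prognostic factor in neurosurgical as well as neurological patients. The clinician knows the surgical diagnosis before any copeptin result, so independence from diagnosis is the least such a claim needs. A variable that is not listed cannot enter the univariate screen or the model that follows it.

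The Introduction gives grounds to expect that copeptin varies with diagnosis. It names stroke and hemorrhage as strong stimuli to ADH release, and says that ADH is stored in and released from the neurohypophysis, which bears on pituitary surgery. If outcome also differs by indication, copeptin can be associated with outcome across the surgical cohort while adding nothing within any diagnosis.

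There is a practical problem too. Where TOAST class and vascular territory are undefined, surgical patients either drop out as incomplete cases or fall into a not-applicable category. That category acts as a hidden cohort label and does not separate the six indications.

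**Working it through.** **1. The Protocol's own figures.** The list counts to 18: age, sex, NIHSS/GCS (3); comorbidities (8); location, TOAST, thrombolysis (3); glucose, CRP (2); temperature, smoking (2). Then 18 x 10 = 180, 18 x 15 = 270 and 18 x 20 = 360, as stated. Accrual: 480 x 0.80 x 0.90 = 345.6, against about 350 stated. Both reproduce.

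**2. Surgical cohort.** From the eligibility table in Section E, 180/480 = 37.5% of the pool is surgical. Expected with follow-up: 180 x 0.80 x 0.90 = 129.6, about 130.

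**3. Mechanism in its simplest form (assumed inputs).** Take two equal groups of indications, with copeptin d SD higher in the high-risk group and no effect within either. With p and q the high-risk share among patients with and without an unfavorable outcome,

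AUC = 0.5 + (p - q) x (Phi(d/sqrt 2) - 0.5).

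- Risks 10% and 40%, d = 0.5: p = 0.40/0.50 = 0.80; q = 0.60/1.50 = 0.40; AUC = 0.5 + 0.40 x 0.138 = 0.555.
- Risks 5% and 50%, d = 1.0: p = 0.50/0.55 = 0.909; q = 0.50/1.45 = 0.345; AUC = 0.5 + 0.564 x 0.260 = 0.647.

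This is the crude AUC. The planned model also adjusts for severity, so a second check is needed.

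**4. Six indications, with and without adjustment (assumed inputs).** Simulation of 130 patients, 2,000 runs per scenario, likelihood-ratio test at two-sided 0.05. Assumed shares: pituitary 20%, ICH 15%, SAH 20%, chronic subdural 25%, trauma 15%, abscess 5%. Copeptin has no effect within any indication; a GCS-like severity score is partly tied to indication. The risks shown are at the indication's average severity.

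| Differences between indications | Risk of unfavorable outcome | Copeptin range | Mean AUC | Significant, crude | Adjusted for severity | Severity and indication |
|---|---|---|---|---|---|---|
| None in risk | 35% | 2.7-fold | 0.50 | 5% | 8% | 6% |
| Mild | 25-48% | 1.8-fold | 0.53 | 9% | 6% | 6% |
| Moderate | 17-60% | 2.7-fold | 0.60 | 48% | 25% | 6% |
| Strong | 11-71% | 5-fold | 0.69 | 97% | 85% | 6% |

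The column that matters for the planned model is the severity-adjusted one: 6% to 85%, depending wholly on the assumptions. Adding indication brings the rate close to nominal in every scenario.

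**5. What the surgical cohort can carry.** Without the three stroke items, 15 predictors remain. Patients per term:

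- 18 listed predictors: 129.6/18 = 7.2.
- 15 usable predictors: 129.6/15 = 8.6.
- 15 + copeptin + 5 indication terms = 21: 129.6/21 = 6.2.

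All are below the Protocol's minimum of 10, which allows 129.6/10, about 12 terms. If 20% to 50% have an unfavorable outcome (assumed), there are 26 to 65 events, or 1.2 to 3.1 per term with 21 terms.

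**6. AUC within an indication group.** In a low-risk half of 65 patients with 5% to 10% unfavorable outcomes (assumed), take 3 to 6 events. The null standard error is sqrt((n1 + n0 + 1)/(12 n1 n0)): sqrt(66/(12 x 3 x 62)) = 0.172 and sqrt(66/(12 x 6 x 59)) = 0.125. The 95% half-widths are 0.34 and 0.24, too wide to be useful.

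**The case against.** The strongest reply is that the planned analysis is multivariable, with age, GCS, comorbidities, glucose, CRP and temperature, and these will absorb much of the difference between diagnoses. That stands in part: severity adjustment brought the mild scenario to 6%, but left 25% and 85% in the other two.

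Second, the stroke and surgical questions are posed separately, the severity item is already adapted by cohort, the study calls itself exploratory, and covariate coding is often left to a statistical analysis plan. But the Protocol does not leave the list open. It fixes 18 named items twice and derives the sample size from them. Lesion location might be read more widely, but its example and the baseline section tie it to ischemic syndromes.

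Third, the surgical question speaks of prognostic accuracy, for which a crude AUC is a fair description. That is so, but it does not support the claim of independent association.

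A reader might go further and infer three things that the documents do not support:

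- That GCS sits near its ceiling in elective or subacute indications. The Protocol gives no GCS distribution.
- That elective patients would supply pre-operative samples and emergency patients post-operative ones. The Protocol describes an extra tube "asserved during the respective routine blood samplings", and the risk section speaks of each routine sampling, so serial samples are possible. Which one serves as the prognostic value is a separate question.
- That TIA patients create the same fault in the stroke model. The overall hypotheses refer to neurological patients, which can include TIA, and TIA patients are identifiable through the ABCD score. Excluding them is a choice of target population.

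**Conclusion.** The point holds in a limited form. The predictor list contains three items that do not serve most surgical patients and leaves out the indication for surgery. Followed as written, the plan cannot show that copeptin predicts outcome in the roughly 130 surgical patients independently of a diagnosis already known. The claims of independent association and of a reliable prognostic factor would not follow for neurosurgical patients.

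It would be tempting to conclude that a positive copeptin result in this cohort would be mostly spurious. The documents do not support that. They give no case mix, outcome rate or copeptin level by indication, and the Introduction makes a difference in copeptin plausible without showing one among the six diagnoses. The simulated rates rest on assumed inputs and show only that the bias can be anything from negligible to large after severity adjustment. The Protocol's sample size arithmetic is not in question.

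**What to change.** In 2.2.2 Statistical Analyses and in Section E, give the neurosurgical model its own short prespecified predictor list:

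- Drop vascular territory, TOAST subtype and thrombolysis.
- Add indication for surgery, grouped into, say, two or three prespecified categories, and keep it in the model without univariate screening.
- Report copeptin's added value over indication, GCS and age.

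A separate AUC within each indication need not be required, given the imprecision shown above.

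Indication is already known from eligibility, so no new data are needed. The cost is a shorter list. Copeptin, GCS, age and two terms for three indication groups make 5 terms. At 10 patients per term about 12 fit, which leaves room for about 7 of the 13 other usable predictors. On the assumed 26 to 65 events, the 5 core terms alone have 5.2 to 13 events each, which argues for adding few. Grouping also leaves some confounding by diagnosis within groups, so the grouping should put indications with similar expected outcome together and be fixed before copeptin is measured.
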